### Study objectives and endpoints

#### Sample size estimation

The main primary and secondary analyses will follow a modified intention-to-treat approach to define the full patient analysis set, based on all randomly assigned patients except those withdrawing consent for use of all trial data and those not fulfilling inclusion criteria and never receiving the intervention.

#### Primary outcome

The primary outcome is the difference between eGOS in patients allocated to Ronopterin and patients allocated to placebo at 6 months after the injury. The eGOS value is determined by a face-to-face meeting; telephone interviews are not planned. Face-to-face meetings allow more accurate and reliable evaluation of the eGOS.

##### Secondary outcomes and pre-specified covariates

Secondary efficacy endpoints are evaluated according to the following priority:
Quality of Life after Brain injury (QOLIBRI) score at 6 months after TBIQOLIBRI overall scale (QOLIBRI-OS) score at 6 months after TBIeGOS at 3 months after TBIQOLIBRI-OS score at 3 months after TBITherapy intensity level (TIL) at 24 h over 14 days after TBINumber of craniectomies (one or both hemispheres)

Further efficacy endpoints for efficacy are:
Mortality at 6 months after TBIIntracranial pressure (ICP) and cerebral perfusion pressure (CPP) over 5 days after TBIIndividual domains of QOLIBRITissue oxygen pressure (PtiO_2_) in cerebral tissue (in centres with respective equipment)Cerebral extracellular glucose, lactate, pyruvate by microdialysis (in study centres with respective microdialysis equipment) on an hourly basis over 5 days. Additionally, glycerol, urea and glutamate in study centres with respective multi-channel microdialysis equipmentPrognostic factor

### Sample size and power

In the NOSTRA phase II study, an odds ratio for the eGOS of 25.2 in favour of Ronopterin was estimated using ordinal logistic regression with a lower (two-sided) 95% confidence limit of 3.2 [9]. For the sample size estimation in the current NOSTRA phase III study, an odds ratio of 2.3 was assumed, which can be considered as very conservative compared to the preceding estimates. In addition, the following distribution of eGOS relative occurrences across the levels for patients in the placebo group was assumed starting from level 1 to level 8: 0.09, 0.1, 0.1, 0.15, 0.3, 0.25, 0.005 and 0.005. This is a smoothed distribution reflecting the actual distribution in the placebo group in the NOSTRA II study. Sensitivity considerations have shown that the sample size estimation is rather robust against deviations from the aforementioned assumed distribution in the placebo group. In a simpler data situation dichotomized as 50% of the patients on placebo, an odds ratio of 2.3 approximately corresponds to an increase of favourable responses under treatment of 20%.

In the present study eGOS is also the primary parameter of analysis; randomisation was planned in a patient number ratio of 1:1 to achieve maximum statistical power. It was assumed that the treatment effect of Ronopterin compared to placebo would be tested on a two-sided alpha level of 0.05 using the non-parametric Wilcoxon rank-sum test for ordered categorical data. Derived from the NOSTRA phase II trial, the phase II/III trial was designed to detect a treatment effect of an odds ratio of 2.3 (approximately 10-fold lower as in the phase II trial) as statistically significant on an alpha level of 0.05 with statistical power slightly > 90% (92.2%); 220 evaluable patients are needed for the statistical intention-to-treat analysis in the full analysis set (FAS). With this number of 220 patients a lower odds ratio of 2.0 would still be detected with 80% statistical power (alpha = 0.05, two-sided) while a higher odds ratio of 2.6 could be detected with 90% power even at a two-sided alpha level of 0.01. To account for withdrawals and patients lost to follow up, the number of patients to recruit has been increased by 5% to 232 patients.

These conservative assumptions on the odds ratio are not unreasonably low, because the treatment effect may be diluted by premature infusion terminations and by missing eGOS values on follow up; such protocol violators are included in the FAS but excluded from the per-protocol set. Under favourable conditions the study has a good chance to demonstrate statistical significance even at the lower alpha level of 0.01 and thus to deliver strong statistical evidence of efficacy.

### Statistical analysis

The null hypothesis of no shift across the eight ordered categories of eGOS for the two treatment groups will be tested based on a proportional odds model stratified by age (18–39 years and 40–60 years). The treatment effect will be estimated using ordinal logistic regression as the (proportional) odds ratio of Ronopterin versus placebo with a two-sided Wald 95% confidence interval. Treatment and age (18–39 years and 40–60 years) will be included in the model. The proportional odds assumption will be tested using the chi-square score test. If the proportional odds assumption is not be fulfilled then the individual cumulative odds ratios will be presented with their 95%-confidence intervals.

The interim analysis is to be conducted after half the patients have completed their 6-month assessment (110 patients in the FAS). The proportional odds model stratified by age is used to compare the groups and the associated *p* value, *p*_1_
*p*_1_ is calculated. If the study continues to the end, the proportional odds model stratified by age based on data from patients randomised in the second stage is used to compare the groups and the associated *p* value, *p*_2_ is calculated. According to Bauer and Koehne [14] and Lehmacher and Wassmer [15], the *p* values are combined to control the type I error. If *p*(*p*_1_*p*_2_) is < 0.025, then significance can be claimed.

The efficacy of Ronopterin will be considered to be proven if the null hypothesis for the primary endpoint is rejected and if the treatment difference is in favour of Ronopterin in the sense of a shift to higher eGOS categories under Ronopterin.

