### Data monitoring and interim analyses

An independent Data and Safety Monitoring Committee (DMC) monitors the quality of the trial and has access to trial outcome and accumulated safety data, including serious adverse events (SAEs), suspected unexpected serious adverse reactions and mortality. In addition, the DMC will review the safety data from a clinical and safety point of view on an on-going basis (Appendix 4).

Three safety interim analyses will be scheduled: when 40, 80 and 110 patients, respectively, have completed their 14-day clinical observation phase. When 110 evaluable patients in the FAS have received their final assessment of clinical outcome (6-month eGOS), an unblinded interim analysis will be conducted by an unblinded statistician and reviewed by the DMC based on clean data on the primary and secondary target variables and on the latest status of safety data. The outcome of this interim analysis will result in one of three possible recommendations of the DMC to the Sponsor to do one of the following:

Stop the study because of futilityContinue and finalize the study as plannedContinue the study as planned but increase the sample size to a specified number of patients

There is no intention to stop the study in the interim if the data already show significant outcome differences between Ronopterin and placebo. An increase in sample size will be recommended by the DMC guided by conditional power of 90%, based on the current estimate of the treatment effect. The maximum sample size to be considered is 330 patients.

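### The Wald 95% interval for the primary odds ratio does not invert the stage-wise combination test that decides significance, so the two can disagree; the confirmatory decision itself is unaffected

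*Protocol article*

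**What the plan says.** Under Statistical analysis, the protocol article gives one effect measure for the primary endpoint: the proportional "odds ratio of Ronopterin versus placebo with a two-sided Wald 95% confidence interval", from an ordinal logistic model with treatment and age group. No stage term or stage weighting is named.

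The same section decides significance by another route. The interim takes place at 110 patients in the full analysis set and yields p1. A second p value is "based on data from patients randomised in the second stage is used to compare the groups", and the two "values are combined to control the type I error". If the combined value "is < 0.025, then significance can be claimed". Two papers on combination tests are cited, but the text does not say which function is used, with what weights, or whether p1 and p2 are one-sided.

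Under Data monitoring and interim analyses, "an unblinded interim analysis will be conducted by an unblinded statistician". The data monitoring committee may recommend stopping for futility (no threshold is given), continuing, or raising the sample size, an increase being "guided by conditional power of 90%, based on the current estimate of the treatment effect". The limit is fixed: "The maximum sample size to be considered is 330 patients". There is no early stop for efficacy.

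**The concern.** A 95% interval is normally read as the set of odds ratios that the test at the matching level does not reject. That link is broken here. The ordinary Wald interval treats all patients as one fixed-size sample and weights the stages by their information. A combination test gives each stage a contribution that does not follow the final stage sizes. If N is raised, stage 2 counts for more in the pooled fit than in an equal-weight combination. If the function is the product of p values, the rejection region has a different shape from the pooled one even when N stays at 220.

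At stake is the presentation of the main result. A report could show a failed primary test beside an interval that excludes no effect, or a successful test beside an interval that includes it. The article does not say how such a result is to be presented.

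**Working it through.** **Inputs from the article.** Placebo eGOS distribution, design odds ratio 2.3, 220 evaluable patients and 1:1 allocation (Sample size and power); interim at 110, stage 2 patients only in p2, threshold 0.025 (Statistical analysis); 90% conditional power at the observed effect, maximum 330, so stage 2 has 110 to 220 patients (Data monitoring and interim analyses).

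**Assumptions, because the article does not fix them.** The 0.025 is one-sided. The function is either inverse normal with equal weights or Fisher's product with critical value 0.0038. N is raised either in every case where the rule asks for it, or only when conditional power is at least 30%. There is no futility stop unless one is stated.

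**1. The plan's own figure.** The Wilcoxon calculation with tie-corrected null variance gives 92.0% power at odds ratio 2.3; the article states 92.2%. The proportional-odds formula V = N(1 − Σp̄³)/12 gives 220 × 0.0776 = 17.08. Power is then Φ(ln 2.3 × √17.08 − 1.96) = Φ(1.48) = 93.1%. The information scale is sound.

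**2. Formulas.** With information I1 and I2 (0.0785 per patient at odds ratio 1.5):
- Pooled log odds ratio: (z1√I1 + z2√I2)/(I1 + I2), standard error 1/√(I1 + I2).
- Inverse normal: Z = (z1 + z2)/√2, significant if Z > 1.96.
- Fisher: with P = p1·p2, combined p = P(1 − ln P).
- Stage 2 size for 90% conditional power: 110 × [(1.96√2 − z1 + 1.28)/z1]², held to 110–220.

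**3. Examples.**
- *No increase, product test.* z1 = z2 = 1.4, N = 220. Estimate 0.476, standard error 0.241: odds ratio 1.61, Wald interval 1.005 to 2.58. P = 0.0808² = 0.00652; combined p = 0.039, not significant. Inverse normal gives 0.024 and agrees with the interval.
- *Increase, interval excludes 1, test fails.* z1 = 1.0: the rule asks for 110 × 3.05² ≈ 1,025, so stage 2 is capped at 220. With z2 = 1.75 the estimate is 0.394 and the standard error 0.196: odds ratio 1.48, interval 1.01 to 2.18. Z = 2.75/√2 = 1.94, p = 0.026; Fisher p = 0.039. Neither is significant.
- *Increase, interval includes 1, inverse normal succeeds.* z1 = 1.6: the rule asks for 110 × 1.53² ≈ 259, capped at 220. With z2 = 1.2 the estimate is 0.374 and the standard error 0.196: interval 0.99 to 2.14. Z = 2.8/√2 = 1.98, p = 0.024, significant.

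**4. How often interval and test disagree** (2 million simulated trials per scenario, normal approximation, no futility stop):

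| N raised | Function | OR 1.5 | OR 2.0 | OR 2.3 |
|---|---|---|---|---|
| In every case | Inverse normal | 4.0% | 1.4% | 0.4% |
| In every case | Fisher | 7.6% | 3.0% | 1.0% |
| Conditional power ≥ 30% | Inverse normal | 0.7% | 0.2–0.3% | 0.1% |
| Conditional power ≥ 30% | Fisher | about 6% | about 3% | about 1.4% |

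With an assumed futility stop at conditional power below 10 to 20%, the Fisher figure at odds ratio 1.5 falls to about 5 to 6%. With inverse normal and N raised in every case, 3.3 of the 4.0 points at odds ratio 1.5 are intervals that exclude 1 although the test failed. When increases are restricted, the small remainder runs mostly the other way.

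**5. Coverage of the Wald interval.** Without futility stopping it is about 94.7 to 95.2%. At odds ratio 1, with N raised in every case, the interval excludes 1 in favour of Ronopterin in 2.8% of trials, against 2.5% for the combination test. With an assumed futility stop at conditional power below 10 or 20%, coverage at odds ratio 2.3 is 93.6 or 93.9%. An interval that inverts the inverse normal test then covers 93.8 or 94.1%, so that shortfall comes from the stopping.

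**The case against.** The strongest reply is that the interval decides nothing. The article considers efficacy proven when the null hypothesis is rejected and the difference favours Ronopterin, and rejection rests on the combination test. This stands. A reader might infer from the 2.8% that the trial's false-positive rate is inflated; the documents do not support that.

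A reader might also infer serious undercoverage from the 93.6 to 93.9% at odds ratio 2.3. That rests on a futility threshold the article does not give, and a test-based interval hardly changes it. Without futility stopping, Wald coverage at 2.3 is about 95.2%. Under the null with the assumed stop, the interval excludes 1 in favour of Ronopterin in only 2.0 to 2.2% of trials. A claim of material miscalibration fails.

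The larger inverse normal disagreement depends on raising N even after a weak interim result, and it peaks at odds ratio 1.5, below both effects (2.0 and 2.3) for which the article quotes power at N = 220 and two-sided alpha 0.05. This too stands. It does not remove the Fisher mismatch, which needs no increase.

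Finally, the article does not state outright that the final fit pools both stages, and an analysis plan that is not shown may add a matched interval. Pooling is the natural reading, though, and the type of interval is a choice the article itself states.

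**Conclusion.** The point holds as an inconsistency between the stated interval and the stated test. It is of low severity, a matter of reporting and not of error control. With inverse normal, disagreement reaches 4.0% of trials at odds ratio 1.5 if N is raised in every case without futility stopping, and at most about 0.7% if N is raised only at conditional power of 30% or more. With Fisher's product it is about 5 to 8% at odds ratio 1.5 and about 1 to 1.5% at 2.3. These figures rest on a one-sided reading of 0.025, equal weights for the inverse normal function, and a final model fitted to all patients. If p1 and p2 were two-sided, 0.025 would not correspond to a 95% interval at all.

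**What to change.** State the combination function, its weights and the sidedness of p1 and p2. Then obtain the primary 95% interval and a median-unbiased estimate by inverting that same function over the log odds ratio. For the equal-weight inverse normal the limits are (Z ± 1.96)/d with d = (√I1 + √I2)/√2. In the z1 = 1.0, z2 = 1.75 example this gives 0.997 to 2.18, in agreement with the non-significant test. Without futility stopping this interval covers 95.0% at every odds ratio tried.

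The function must match. If the product test is the one prespecified, an inverse normal interval would disagree with it in 8.1% of trials at odds ratio 1.5, no better than the Wald interval (7.6%); the product test itself must then be inverted.

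Keep the pooled Wald interval, labelled descriptive. The cost is a little programming and possibly a slightly wider interval; sample size, conduct and the test do not change. The change does not address any coverage loss from futility stopping.

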### Secondary efficacy analysis

The eGOS variable at 3 months will be analysed using ordinal logistic regression as the (proportional) odds ratio of Ronopterin versus placebo with a two-sided Wald 95% confidence interval. Treatment and age (18–39 years and 40–60 years) will be included in the model. The proportional odds assumption will be tested using the chi-square score test.

The Quality of Life after Brain Injury Index (QOLIBRI) [16] score will be reported at 6 months after TBI. The QOLIBRI overall scale (QOLIBRI-OS) score will be reported at 3 and 6 months after TBI. The total score on the QOLIBRI and QOLIBRI OS will be analysed by analysis of variance (ANOVA) including treatment, age category (18–39 years and 40–60 years) and treatment-by-age interaction as covariates. The adjusted mean difference in the total scores under Ronopterin and placebo, with the 95% confidence interval, will be used as the treatment effect estimate.

The therapy intensity level (TIL) as a measure of intensity of treatment [17] from day 1 to day 14 post trauma will be analysed using a mixed model for repeated measures including treatment, age category (18–39 years and 40–60 years), days, treatment-by-age and treatment-by-day interaction as fixed effects and patient as a random effect. Using these methods, TIL will be analysed across the whole observation period from day 1 to day 14. Treatment effect estimates will be based on adjusted mean differences including 95% confidence intervals.

The number of craniectomies (one or both hemispheres) will be analysed using a generalized linear model - Poisson as the distribution, with treatment, age category (18–39 years and 40–60 years) and treatment-by-age interaction as factor. The estimated mean difference of the natural logarithms with the 95% confidence interval for the mean difference will be used to estimate the treatment effect. The ratio of the mean number of craniectomies per day and its 95% confidence interval can be estimated by transforming the aforementioned estimated mean difference and its 95% confidence interval by the exponential function.

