### Trial interventions

The intervention is the intravenous administration of Ronopterin compared to a placebo (0.9% saline) via central venous catheter. A total dose of 17 mg/kg b.w. of Ronopterin is infused over 48 h (daily dose 8.5 mg/kg b.w.). The study drug or placebo is administered over 48 h at the earliest 6 h after injury and at the latest 18 h after the injury.

In the case that serum creatinine values increase by more than 50% from the preceding measurement, the infusion has to be stopped. Any other renal safety parameters that indicate renal deterioration may also cause the infusion to be stopped.

The administration period is followed by a clinical follow-up period of 14 days. Patients are closely monitored in the first three days after the end of the infusion. The clinical period is followed by a post-clinical period with visits at 3 and 6 months (Fig. 1).

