### Further efficacy analysis

Tertiary endpoints will be delineated descriptively and/or tested two-sided in the sense of exploratory data analysis; there will be no alpha correction for these endpoints. The proportions of patients who die will be compared at 6 months after TBI. The estimate of the difference in proportions (Ronopterin versus Placebo), 95% confidence interval and Chi-square *p* value will be calculated. In the case of lower cell frequencies (< 5), the Fisher exact test will be used instead.

Overall survival will be analyzed by log-rank test. Kaplan-Meier estimates of the 25th, 50th and 75th quartiles will be reported. The 95% confidence interval for the median and *p* values will also be calculated.

Absolute values of ICP and CPP (until day 5) will be summarized per treatment group and for each time point by means of descriptive statistics. The 95% confidence intervals will be calculated for the median using non-parametric methods for order statistics.

The comprehensive QOLIBRI assesses health-related quality of life (QoL) within six domains (self-cognition, cognition, daily life and autonomy, social relationships, emotions and physical problems). Total scores in each of these domains of QOLIBRI will be analysed using the *t* test with a two-sided alpha level of 0.05. The mean difference in the scores and the 95% confidence interval under Ronopterin and placebo will be used as the treatment effect estimate.

Partial brain oxygen pressures are recorded every 1 h up to 5 days after the start of the infusion. Absolute values will be summarized per treatment group and for each time point by means of descriptive statistics. The 95% confidence intervals for the mean will be calculated (normal approximation).

The cerebral glucose, lactate, pyruvate and glutamate are recorded every 1 h up to 5 days after the start of the infusion. Absolute values will be summarized per treatment group and for each time point by means of descriptive statistics. The 95% confidence intervals for the mean will be calculated (normal approximation).

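### ICP and CPP are timed from injury while brain oxygen and microdialysis are timed from infusion start, and the TIL model has no pre-infusion severity covariate: slight dilution and lost precision in non-primary endpoints

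*Protocol article*

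**What the plan says.** **Start of treatment.** Under Trial interventions, study drug or placebo is "administered over 48 h at the earliest 6 h after injury and at the latest 18 h after the injury".

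**TIL.** The list of secondary outcomes counts therapy intensity over 14 days from the injury, with a reference to 24 h. Secondary efficacy analysis says that TIL "from day 1 to day 14 post trauma will be analysed using a mixed model for repeated measures" and that "TIL will be analysed across the whole observation period from day 1 to day 14". Besides treatment and age category, the model terms are "days, treatment-by-age and treatment-by-day interaction as fixed effects and patient as a random effect". No pre-infusion TIL or other severity measure is listed.

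**ICP and CPP.** The outcome list defines both over five days from the injury. In Further efficacy analysis, "Absolute values of ICP and CPP (until day 5) will be summarized per treatment group and for each time point by means of descriptive statistics". That sentence gives no time origin, and no model or between-arm estimate is planned.

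**Other monitoring endpoints.** The same section uses a different clock: "Partial brain oxygen pressures are recorded every 1 h up to 5 days after the start of the infusion", and "The cerebral glucose, lactate, pyruvate and glutamate are recorded every 1 h up to 5 days after the start of the infusion".

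**Prognostic factor.** A baseline prognostic score is planned, also in Further efficacy analysis, but only to compare the arms at baseline.

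**The concern.** There are two separate weaknesses.

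The first is the time axis. With an injury clock and a treatment start spread over 12 hours, the early ICP and CPP summaries in the Ronopterin arm average patients on drug with patients still waiting for it. Those summaries also cannot be lined up hour by hour with brain oxygen or microdialysis, which are counted from infusion start. The Abstract names ICP and CPP among the measures on which an effect is to be assessed, so the early curve should be interpretable.

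The second is precision. The trial admits patients from a Glasgow Coma Score of 3 upward, and the Background blames earlier failed trials mainly on heterogeneity. Even so, the TIL model adjusts only for age below 40 versus 40 and over. Variation between patients that a pre-infusion measurement could explain stays in the residual and widens the confidence interval.

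At stake are the clarity and precision of one secondary endpoint and two tertiary ones.

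**Working it through.** **The plan's own figure.** The article gives no power or sample size for TIL, ICP or CPP, so there is no stated figure to reproduce for this point. The primary-endpoint power does reproduce. With odds ratio 2.3, 220 patients and two-sided alpha 0.05, a Wilcoxon simulation gives 92.5% and the proportional-odds formula 93.1%, against 92.2% stated. Nothing below depends on it.

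**Inputs from the article.** Infusion start h = 6 to 18 h after injury. TIL window 14 days = 336 h from injury. ICP/CPP window 5 days = 120 h from injury. Brain oxygen and microdialysis window 120 h from infusion start.

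**Step 1: ICP/CPP window on the infusion clock.** Hours after infusion start = 120 − h.
- h = 6: 120 − 6 = 114 h
- h = 18: 120 − 18 = 102 h

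The comparison measures cover 120 h. Pre-infusion time is 6/120 = 5% to 18/120 = 15% of the ICP/CPP window, if values are recorded from injury onward. Between 6 and 18 h after injury, treated and not-yet-treated patients fall at the same time point.

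**Step 2: pre-infusion share of TIL.**
- Of day 1: 6/24 = 25% to 18/24 = 75%
- Of the whole window: 6/336 = 1.8% to 18/336 = 5.4%

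This is an upper bound. It applies only if each daily score looks back over the preceding 24 h. If TIL is scored at 24 h after injury, every patient started on time has by then had 24 − 18 = 6 to 24 − 6 = 18 h of infusion, and no score is taken before treatment.

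**Step 3: what that dilution could cost.** Assume a constant effect after infusion start and 80% power for the undiluted 14-day mean (the article gives neither). With a share f of the window untreated, power = Φ[(1.960 + 0.842)(1 − f) − 1.960].
- f = 0.0179: Φ(0.792) = 78.6%
- f = 0.0536: Φ(0.692) = 75.5%

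**Step 4: what a baseline covariate could gain.** If the covariate correlates r with the outcome mean, residual variance is multiplied by 1 − r², which is equivalent to multiplying the sample size by 1/(1 − r²). The values of r are assumptions.

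| r | 1 − r² | variance removed | equivalent sample size |
|---|---|---|---|
| 0.3 | 0.91 | 9% | ×1.10 |
| 0.5 | 0.75 | 25% | ×1.33 |
| 0.6 | 0.64 | 36% | ×1.56 |

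This step applies to TIL, which has a model. For ICP and CPP it would apply only once an adjusted comparison is added.

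**The case against.** The case for leaving the plan alone is substantial, and most of it stands.

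- **No bias.** A reader might infer that counting pre-treatment hours as response biases the comparison. It does not. Randomisation makes those hours comparable between arms in expectation, and chance imbalance is already reflected in the confidence interval.
- **Day 1 is not a pre-treatment value.** It is at most a mixed day, and a score taken at 24 h follows 6 to 18 h of infusion. The treatment-by-day term lets the day-1 difference be seen separately. Dropping day 1 outright would discard treated time from a 48 h infusion.
- **No ICP/CPP model lacks a covariate.** These endpoints are only described, so the precision argument does not touch the analysis as written. A purely descriptive treatment is also allowed for this exploratory tier, and brain oxygen and microdialysis receive the same.
- **The document is a condensed article.** TIL scoring time, baseline definitions and the first recorded ICP hour may be set out in the full protocol or the analysis plan. Nothing shown says that ICP or CPP is summarised for the first 6 h.
- **Low rank.** TIL is fifth of six secondary endpoints, Trial design calls the secondary analyses exploratory, and ICP and CPP are tertiary.

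These arguments do not remove two things that the article itself states: the outcome list and the analysis section put the monitoring endpoints on different clocks, and the TIL model is written out term by term without a baseline or severity value. The adjusted multivariable analyses announced under Trial design name no covariates and do not change that model.

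**Conclusion.** The point holds as a modest, inexpensive improvement. ICP and CPP follow the injury clock while brain oxygen and microdialysis follow the infusion clock, leaving 102 to 114 h of post-start observation against 120 h and a mixed interval from 6 to 18 h after injury. The TIL model gives up precision by omitting any pre-infusion severity measure.

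Dilution of TIL is at most 1.8 to 5.4% of the window, and possibly nil, depending on how the score is taken. The avoidable variance is 9 to 36% for an assumed r of 0.3 to 0.6; the documents give no correlation, so this is a range and not an estimate for this trial.

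It would be tempting to conclude that the trial cannot show whether Ronopterin affects ICP, CPP or therapy intensity, or that the monitoring endpoints cannot be read together. The documents do not support that. The windows share 102 to 114 of 120 h, and the TIL comparison remains valid. Type I error is not inflated and the primary eGOS analysis is unaffected.

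**What to change.** Before unblinding, amend the analysis wording as follows.

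1. **ICP and CPP.** Use infusion start as time zero, as already done for brain oxygen and microdialysis. Label values before it as baseline. Add an exploratory baseline-adjusted difference between arms with a 95% confidence interval.
2. **TIL.** Add one pre-infusion covariate to the mixed model: baseline TIL if it was recorded, otherwise pre-infusion ICP or the baseline prognostic factor that is already planned.
3. **TIL day 1.** State whether the score is taken at a time point or looks back over the day. Keep day 1 in the model, where the treatment-by-day term can show it separately, unless it is a look-back score that covers pre-infusion hours.

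The cost is a derived time variable and a few sentences. Injury and infusion-start times are needed anyway to apply the 6 to 18 h window, and pre-infusion ICP should be obtainable because catheter placement is an inclusion criterion. The drawback is reliance on a proxy covariate if no pre-infusion TIL exists; a weaker correlation then brings a smaller gain. Sample size, visits and the primary analysis do not change.

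### Craniectomy counts: the model as listed estimates a ratio per patient but is reported as per day, and Poisson standard errors need not fit a count of 0, 1 or 2

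*Protocol article*

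**What the plan says.** The section Secondary outcomes and pre-specified covariates lists six secondary efficacy endpoints in order of priority. The number of craniectomies is the sixth.

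Under Secondary efficacy analysis the article states: "The number of craniectomies (one or both hemispheres) will be analysed using a generalized linear model - Poisson as the distribution". The model is specified "with treatment, age category (18–39 years and 40–60 years) and treatment-by-age interaction as factor". The effect measure is "The estimated mean difference of the natural logarithms with the 95% confidence interval for the mean difference". The reported quantity is "The ratio of the mean number of craniectomies per day", with its confidence interval, obtained by applying the exponential function to that difference.

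The paragraph just before, on therapy intensity level, handles time explicitly. It names a day 1 to day 14 window, and its model contains "days, treatment-by-age and treatment-by-day interaction as fixed effects and patient as a random effect".

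**The concern.** Two things do not fit.

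First, the label does not match the listed model. A log-linear model for a per-patient count, with no time term, yields after exponentiation a ratio of means per patient. A ratio per day needs time at risk in the model. The neighbouring therapy intensity model shows that days are named where they are meant to enter.

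Second, the Poisson distribution ties the variance to the mean. The endpoint is described by one or both hemispheres, which reads most plainly as 0, 1 or 2 per patient. A count bounded like that has its own variance, which equals the mean only at particular combinations of incidence and bilateral share. Model-based standard errors are then too large or too small.

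At stake are the calibration of the interval and p value for this endpoint, and whether a reader can tell what the reported ratio means.

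**Working it through.** **Inputs from the article.** 220 evaluable patients allocated 1:1, so n = 110 per arm (Sample size and power; Randomisation). The terms, effect measure and label are as quoted above. The article gives no figure for craniectomies, so there is none to reproduce.

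**Inputs assumed.** The incidence p of any craniectomy, the share b of operated patients counted as two, and the mean days at risk per arm. The article gives none of these. The maximum of two per patient is inferred from the endpoint's wording.

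**1. Standard errors.** With equal arms and per-patient mean μ and variance V:

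- Poisson model: SE of the log ratio = √(2/(nμ))
- True: SE of the log ratio = √(2V/(nμ²))
- Ratio, model to true = √(μ/V), which does not depend on n
- True size of a nominal 5% two-sided test = 2·(1 − Φ(1.96·√(μ/V)))

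For counts of 0, 1 or 2: μ = p(1+b) and V = p(1−b) + 4pb − μ².

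Yes/no example, p = 20%, b = 0: the model SE is √(2/(110·0.20)) = 0.3015. The true SE is √(2·0.80/(110·0.20)) = 0.2697. The ratio is 1.118 and the size 2.8%.

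Example with p = 10%, b = 20%: μ = 0.12, V = 0.08 + 0.08 − 0.0144 = 0.1456, V/μ = 1.213. The ratio is 1/√1.213 = 0.908 and the size 7.5%.

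| Assumed incidence | None counted as two | 10% of operated count as two | 20% of operated count as two |
|---|---|---|---|
| 10% | 1.05 (3.9%) | 0.97 (5.8%) | 0.91 (7.5%) |
| 20% | 1.12 (2.8%) | 1.02 (4.6%) | 0.96 (6.1%) |
| 30% | 1.20 (1.9%) | 1.08 (3.4%) | 1.01 (4.7%) |

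Each cell shows model SE divided by true SE, with the true size in brackets. Setting V = μ gives p = 2b/(1+b)², the incidence at which the Poisson SE is exactly right: 0.2/1.21 = 16.5% for b = 10%, and 0.4/1.44 = 27.8% for b = 20%. Below that incidence the SE is too small, above it too large.

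**2. Per patient against per day.** The per-day ratio equals the per-patient ratio times (mean days at risk on placebo ÷ mean days at risk on Ronopterin). For a per-patient ratio of 1.00:

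- 14 and 14 days: 1.00
- 12.5 and 13.3 days: 12.5/13.3 = 0.94
- 12 and 13.5 days: 12/13.5 = 0.89

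**3. Check on simulated data.** One simulated trial of 220 patients had a yes/no outcome at 20% and the three listed terms. Adding the same offset, log(14), for every patient left the treatment coefficient (0.138) and its SE (0.421) unchanged. A sandwich variance gave an SE of 0.376. The ratio 0.421/0.376 = 1.12 agrees with the formula.

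**The case against.** The best defence is that this is a journal article standing in for a longer protocol. An offset, a scale parameter or a robust variance may be stated in the full document or the analysis plan. The sentence lists factors, and an offset is not a factor; the per-day wording may even show that an exposure term was intended. This stands to the extent that the absence of such details is not itself the finding. What remains is that the listed terms and the stated quantity do not match within one paragraph.

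It is also fair that a common observation window makes the two ratios identical, so the label alone does not make the number wrong. A reader might infer that the reported ratio is numerically wrong, but that would need time at risk to differ between arms. Deaths could cause this: the sample-size section puts 9% of placebo patients in the lowest eGOS level, read here as death. The article gives nothing on time at risk, however.

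Two stronger readings are tempting and not supported. One is that the Poisson standard errors are simply too large, so the analysis is at worst conservative. That holds for a pure yes/no outcome. With bilateral procedures counted as two, the direction can reverse, and the article gives neither incidence nor bilateral share. The other is that, with the interaction in the model, the reported effect describes one age group only. That would need reference coding and a report of the raw coefficient. The text refers to an estimated mean difference on the log scale, and the same section uses adjusted mean differences for quality of life and therapy intensity. The natural reading is a contrast averaged over age groups.

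Finally, the endpoint ranks last of six, and proof of efficacy rests on the primary endpoint alone. That stands and limits the weight of the point.

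**Conclusion.** The point holds, as a minor one. The model as listed estimates a ratio of mean craniectomies per patient, and the per-day label is justified only if mean time at risk is equal between arms. This mismatch rests on the text alone. How far the two ratios could differ depends on assumed days at risk: 0.94 or 0.89 in place of 1.00 in the illustrations above.

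The Poisson variance is not in general right for a count of 0, 1 or 2. Over assumed incidences of 10-30% and bilateral shares of 0-20%, the model SE runs from about 9% too small to 20% too large, and the true size of a nominal 5% test from about 7.5% down to 1.9%. No direction can be claimed without the incidence and the bilateral share. These figures also rest on the inferred maximum of two and on no robust variance or scale parameter being specified elsewhere. The primary conclusion is not touched.

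**What to change.** **Variance.** Keep the count model and use a robust (sandwich) variance. Alternatively, analyse any craniectomy (yes/no) by logistic or modified Poisson regression with treatment and age group, and tabulate bilateral procedures. The first option leaves the endpoint as defined, and nothing in this point requires removing the interaction from that model. The second is easier to interpret but drops the distinction between one and two craniectomies from the test, so it changes the form of the endpoint.

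**Label.** For the count model, report a ratio of mean craniectomies per patient; if a per-day rate is wanted, name the time at risk and add its logarithm as an offset. For the yes/no analysis, report an odds ratio or a risk ratio per patient.

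**Cost.** A few lines of analysis-plan text and slightly more analysis work, settled before unblinding. If the full protocol or analysis plan already specifies an offset or a robust variance, that item needs only a check that text and label agree.
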